### Treatment of MF and SS

The treatments will be given according to clinical routine and national and international guidelines for MF and SS and participation in this study will not affect the choice of treatments. Ongoing treatments will be documented.

### Blood Samples for Soluble Interleukin-2 Receptor, Interleukins, and Thymus and Activation-Regulated Chemokine/CCL17

Blood samples in patients will be analyzed for complete blood count, liver and kidney function, lactate dehydrogenase, soluble interleukin-2 receptor, interleukin-6, interleukin-8, interleukin-10, and thymus and activation-regulated chemokine/CCL17 (Multimedia Appendix 1).

### Blood Samples for Analysis of Immunoglobulin E Against Specific Antigen

Total immunoglobulin E and specific immunoglobulin E for *S. aureus* enterotoxin A (m80), enterotoxin B (m81), toxic shock syndrome toxin-1 (Rm226), *Malassezia* (m227), and *Candida albicans* (m5) will be analyzed in patients and in the control group (Multimedia Appendices 1 and 2, respectively).

### Blood Samples for Analysis of Lymphocyte Subpopulations

Flow cytometry of peripheral blood will be performed in patients to analyze the T-cell subpopulations including naive, effector, and memory T-cells (including Th1, Th2, and Th17 cells) and activated and regulatory T-cells. Monoclonal antibodies recognizing CD4, CD8, CD197, CD45RA, CD25, CD194, CD127, CD45RO, CD183, and CD196 will be used [28]. In addition, to evaluate the presence of clonal T-cells in peripheral blood and biopsies the following panel: T-cell receptor fluorescein isothiocyanate, TRBC1 phycoerythrin, CD16 electron coupled dye, CD2 PC7, CD3 BV421, CD4PC5.5, CD7 A700, CD8 KrO, CD26 allophycocyanine, and CD45 allophycocyanine-H7 will be used [29] (Multimedia Appendices 1 and 3, respectively).

### Serum-Based Profiling of Immune-Related Soluble Proteins

Broad sets of serum-based protein profiling focused on immune-related proteins will be performed in patients. Global protein profiling will be performed using commercially available methods, allowing high-plex analyses of immune-related soluble molecules. State-of-the-art bioinformatic tools will be applied for preprocessing and analysis of data (Multimedia Appendix 1).

### Assessment of Tumor Microenvironment by Digital Spatial Profiling and Single-Cell RNA Sequencing

To allow the study of the cellular tumor immune microenvironment, 2 biopsies from affected skin and 1 biopsy from unaffected skin, at least 5 cm away from affected skin, will be taken. In the control group, 1 skin biopsy is taken from the upper arm. The skin biopsies will be formalin-fixed and paraffin-embedded. In addition, blood will be drawn from patients and healthy controls and peripheral blood mononuclear cells will be cryopreserved.

Multiplex analyses of samples taken before and after progression have the potential to contribute to novel biological knowledge as previously discussed in a recent review by the group Kalliara et al [30] and will be performed in samples collected over time. In brief, in skin biopsies, Digital Spatial Profiling will be performed to study immune infiltration in CTCL and how it evolves during the progression of the disease [31]. Single-cell RNA and T-cell receptor sequencing will be applied to sorted CD3+ cells to follow the evolution of the malignant clone over time. Moreover, additional assessments of genetic and epigenetic changes in the tumor and tumor microenvironment will be performed in skin biopsies (Multimedia Appendix 1).

### Assessment of Epigenetic Factors in Circulating Tumor Cells Compared to Normal and Host T-Cells

Cell sorting of CD3+ cells from peripheral blood in patients with blood involvement will be performed using FACSAria (BD, Bioscience). When possible, 2-3 million cells will be sorted from each patient to allow the preparation of DNA for epigenetic analysis and RNA for gene expression analysis. Analysis of histone modifications and chromatin accessibility will be performed by ChIP-seq (chromatin immunoprecipitation with sequencing) and ATAC-seq (assay of transposase-accessible chromatin with sequencing), respectively. Moreover, molecular profiling using nCounter analysis (NanoString Technologies, Inc) will be performed to profile cells through expression panels focused on immune profiling and proliferative signaling pathways (Multimedia Appendix 1).

### Microbiological Sampling

Microbiological samples will be analyzed from affected skin and from unaffected skin 5 cm away from affected skin, preferably from the upper body, and from nares in patients. In the control group, the microbiological samples will be analyzed from the upper arm and from the nares (Multimedia Appendices 1 and 2, respectively).

### Analysis of Skin Barrier Function

Skin barrier function will be measured as transepidermal water loss (TEWL) with a closed chamber TEWL meter, VapoMeter 300 (Delfin Technologies Ltd), according to guidelines [32]. TEWL will be measured on affected skin and on unaffected skin 5 cm away from affected skin, preferably from the upper body. TEWL will be measured on the upper arm in the control group (Multimedia Appendices 1 and 2).

### Hematopathology of Skin, Lymph Node, Bone Marrow, and Tumor Biopsies

Hematopathology of skin biopsy will be performed in affected skin from patients and is optional from lymph nodes, bone marrow, and tumors (Multimedia Appendices 1 and 3).

### Patient-Oriented Life Quality Measures

Patient-oriented life quality measures will be performed. The Dermatology Life Quality Index [33], Peak Pruritus Numerical Rating Scale [34], Sleep Numerical Rating Scale, and Connor-Davidson Resilience Scale [35] will be used (Multimedia Appendix 1).

### Statistical Analysis

The sample profiles from patients with an early stage of disease (stage IA-IIA) will be compared to samples from patients with an advanced stage of disease (stage IIB-IVB) using multivariate analysis with principal component analysis. Individual samples will be compared between the groups using the Mann-Whitney *U* test. Other translational samples will be presented by descriptive statistics. Progression-free and overall survival will be presented using Kaplan-Meier plots.

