### Prognosis of MF and SS

The TNMB stage at diagnosis remains the most important prognostic factor [9,10]. Many patients with early stages of MF have an indolent disease with a 5-year disease-specific survival of 89% to 98% [8,11]. However, approximately 25% of patients with early stages of disease will later progress to advanced stages [4]. Patients with advanced stages of MF have a 5-year disease-specific survival of 18% to 56% associated with treatment failure [8,10]. The 5-year disease-specific survival of SS is 36% [3,8,10].

Multivariate analyses of cohorts of patients with MF and SS have identified potential adverse prognostic factors in the early stages of disease consisting of male gender, aged >60 years, plaques, folliculotropic disease, and stage N1/NX and negative prognostic factors for advanced disease consisting of male gender, aged >60 years, stages B1/B2 and N2/N3, and visceral involvement [12,13]. The presence of plaque lesions in the early stage of the disease, large cell transformation in the skin, and elevated lactate dehydrogenase are also identified as adverse prognostic factors [11,14,15]. Still, there is an unmet clinical need to identify which patients will progress to an advanced stage of disease, and there is a great need for new reliable prognostic markers.

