### Goals of This Study

The primary objective of this study is to identify serum-protein markers for 6-month progression-free survival (PFS) and to identify the immune cell profile in blood for 6-month PFS.

Secondary objectives are to identify the immune cell profile in the skin for 6-month PFS, analyze the lymphoma microenvironment in the skin for 6-month PFS, identify the skin barrier and skin microbiology profiles for 6-months PFS, and identify the epigenetic changes in lymphoma T-cells and host T-cells for 3 months PFS.

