### Stage of Disease and Modified Severity-Weighted Assessment Tool

Patients will be staged according to the TNMB classification [8]. The extent of disease in the skin will be measured according to the Modified Severity-Weighted Assessment Tool [6,7]. Progression or regression will be defined as a shift from one stage to another.

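### The only named between-group comparison is early versus advanced stage, so it finds markers of stage, while the primary objective asks for markers of 6-month PFS

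*Protocol article*

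**What the plan says.** Under Goals of This Study, the protocol article states: "The primary objective of this study is to identify serum-protein markers for 6-month progression-free survival (PFS"), and adds a second part, "to identify the immune cell profile in blood for 6-month PFS". Most secondary objectives use the same 6-month endpoint.

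The Statistical Analysis section then names these analyses:

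- Multivariate: profiles of the early group (IA-IIA), as the article puts it, "will be compared to samples from patients with an advanced stage of disease (stage IIB-IVB) using multivariate analysis with principal component analysis".
- Single markers: a Mann-Whitney test between the same two stage groups.
- Remaining translational material: descriptive only.
- Survival: "Progression-free and overall survival will be presented using Kaplan-Meier plots".

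The Abstract, the Results section and the Principal Findings paragraph of the Discussion frame the evaluation by stage in the same way. Results expects 36 of 120 patients to be in the advanced group.

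Three other statements matter here. The section on staging says: "Progression or regression will be defined as a shift from one stage to another". Results says that patients who cross from early to advanced disease will be analysed individually and as a group. The section on digital spatial profiling and single-cell sequencing plans multiplex work on samples from before and after progression.

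**The concern.** The objective needs an analysis with PFS as the outcome and a marker as the predictor. The stated comparison has stage as the grouping variable and the marker as the outcome, which is a different question.

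The difference matters because the article itself says under Prognosis of MF and SS: "The TNMB stage at diagnosis remains the most important prognostic factor". The same section describes the unmet need as knowing which patients will progress. A marker that merely mirrors stage adds nothing to what staging already tells the clinician. If the stated comparison is what gets reported, proteins associated with stage may be presented as prognostic without evidence of prognostic value beyond stage. A marker that separates progressors from non-progressors within a stage could go unseen. The article also accepts publication of selected translational findings before the main results, so such a report could appear early.

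**Working it through.** **1. Objective against analysis.**

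| Element | Primary objective | Stated analysis |
|---|---|---|
| Outcome | PFS | marker level |
| Explanatory variable | serum protein, blood cell profile | stage group |
| Time point | 6 months | none given |
| Role of PFS | endpoint | Kaplan-Meier plots, no marker mentioned |

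**2. Can stage group stand in for PFS status?** Apply the article's definition of progression as a stage shift:

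- A patient who moves from IA to IB has progressed but stays in the early group.
- A patient in stage IIB who is stable at 6 months is event-free but counts as advanced.

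Both kinds of patient are misclassified if stage group is read as PFS status.

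**3. The article's own figure.** 0.30 × 120 = 36 advanced patients, as stated, leaving 120 − 36 = 84 early. The article gives no significance level, effect size, progression rate or event count, so everything below rests on assumptions made for illustration.

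**4. What the stage test responds to.** Assume normal data and a two-sided 5% level. With the Mann-Whitney efficiency of 0.955, the approximate power at a standardised difference d is Φ(d × √0.955 / √(1/84 + 1/36) − 1.96), where √(1/84 + 1/36) = 0.199.

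- d = 0.5: Φ(2.45 − 1.96) = 0.69 (simulation 0.68).
- d = 0.8: Φ(3.92 − 1.96) = 0.975 (simulation 0.97).
- Difference detectable with 80% power: (1.96 + 0.84) × 0.199 / √0.955 = 0.57 SD.

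**5. Stage marker against progression marker.** Simulation with 2,000 runs per setting and 84 versus 36 patients, under three assumed pairs of 6-month progression risk. The stage test is the Mann-Whitney test. The progression test is a likelihood-ratio test for the marker in a logistic model for 6-month progression, adjusted for stage group.

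| Assumed risk, early / advanced | Marker raised 0.8 SD in advanced stage, no effect within stage: stage test | same marker: progression test | Marker with OR 2 per SD for progression, unrelated to stage: stage test | same marker: progression test |
|---|---|---|---|---|
| 5% / 20% | 97% | 7% | 5% | 60% |
| 10% / 30% | 97% | 6% | 5% | 76% |
| 15% / 40% | 97% | 5% | 5% | 85% |

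The stage test flags the marker without prognostic value within stage almost always, and the genuine progression marker only at the false-positive rate.

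**6. What a PFS analysis could detect.** For one continuous marker, 80% power and a two-sided 5% level, the detectable HR per SD is exp((1.96 + 0.84)/√events). With an assumed 5%, 10%, 20% or 30% of 120 patients progressing by 6 months:

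| Events | Detectable HR per SD |
|---|---|
| 6 | 3.14 |
| 12 | 2.25 |
| 24 | 1.77 |
| 36 | 1.60 |

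These figures make no allowance for testing many markers.

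**The case against.** **Progression is not ignored.** Results plans an analysis of early-to-advanced crossers, the spatial-profiling section plans before-and-after-progression work, and the Discussion says serial sampling is meant to capture changes around progression. A reader might infer from the Statistical Analysis section that progression is never analysed; the article does not support that. What these places lack is a comparator, a statistical method and the 6-month endpoint. The crosser analysis also leaves out shifts within a stage group, and the before-and-after work mainly concerns skin biopsies and sorted CD3+ cells, not the primary serum proteins. They narrow the point without removing it.

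**The section is short and the full protocol is not shown.** A marker-to-PFS model may exist elsewhere, and the text does not say whether the Kaplan-Meier curves will be split by marker. It would therefore go too far to say that the study cannot answer its primary question. The point is limited to what the article does fix: a stated comparison that does not match its stated objective.

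**The percentages are illustrative.** They show that a stage test detects stage differences; they do not measure this study's loss. They also assume full accrual, whereas 18 patients had been enrolled by December 2023. Both remarks stand.

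**PCA is a normal exploratory display.** Agreed. The problem is the grouping variable, not PCA.

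**Events may be too few for modelling.** This limits what can be modelled, above all any multi-marker model, but it does not justify answering a question about stage instead.

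**Conclusion.** The point holds in this form: the one between-group comparison that the article names contrasts stage groups, and PFS is displayed without a stated link to any marker, although the primary objective is markers for 6-month PFS. This rests on the text alone and needs no assumption. By the article's own definition of progression, stage group and PFS status are different things.

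The size is indicative. With assumed normal data, a two-sided 5% level and the article's 84 to 36 split, the stage comparison flags a 0.8 SD stage difference without prognostic value within stage in about 97% of runs (0.5 SD: about 68%), and a progression marker unrelated to stage in about 5%. The contrast with a stage-adjusted progression test also depends on the assumed 6-month risks. It matters because it concerns the primary objective; it can be put right cheaply before the final analysis.

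**What to change.** Make the primary analysis relate each prespecified serum protein and blood-cell subset to progression or death within 6 months. Measure the marker at inclusion, or at a defined landmark sample with allowance for repeated samples per patient. Use a Cox or logistic model stratified or adjusted for early/advanced stage, and report the effect per SD and 6-month PFS by marker level. Keep PCA and the early-versus-advanced tests as descriptive secondary analyses. Treat any penalised multi-marker model as exploratory and dependent on the number of events.

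The cost is a reworded statistical section and some extra analysis work. Sampling and staging every 3 months are already planned, so no further visits are needed. The downside is limited precision if 6-month events are few: at an assumed 5-30% progression there would be 6-36 events and a detectable HR per SD of about 3.1 to 1.6 for a single marker. That is a reason to keep the list of prespecified markers short.

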## Methods

### Study Design

The Predictive and Prognostic Biomarkers in Patients With MF and SS (BIO-MUSE) study is a translational prospective study, aiming to include 120 adult patients with MF and SS and a control group of 20 healthy volunteers (Figure 1). Sampling of each patient will be performed every 3 months for 3 years. The control group will be examined on 3 different occasions at least 2 months apart. This study is presently open at Skåne University Hospital and aims to open at Karolinska University Hospital. The multicenter study design enables other Swedish sites to be included, after further ethical approval.

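### PCA, the only multivariate method named for comparing early and advanced profiles, uses neither stage nor PFS and by itself tests no group difference, so a joint marker profile can be missed or a batch or treatment split misread

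*Protocol article*

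**What the plan says.** In the protocol article, Goals of This Study sets the primary objective: to "identify serum-protein markers for 6-month progression-free survival (PFS) and to identify the immune cell profile in blood for 6-month PFS". The section on serum-based profiling describes commercial methods "allowing high-plex analyses of immune-related soluble molecules", without a number of markers, and refers in general terms to further bioinformatic tools that it does not name.

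The Statistical Analysis section says that profiles from stages IA-IIA and IIB-IVB will be compared "using multivariate analysis with principal component analysis". Three further statements follow:

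- For single measurements, the test is by stage group: "Individual samples will be compared between the groups using the Mann-Whitney" method.
- The remaining translational data are to be summarised descriptively.
- For the outcomes, no model is named: "Progression-free and overall survival will be presented using Kaplan-Meier plots".

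PCA is the only multivariate method named. Study Design gives the target as "aiming to include 120 adult patients with MF and SS and a control group of 20 healthy volunteers", and Results expects about 30% of the patients (36 of 120) to be in the advanced group.

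**The concern.** The objectives ask which set of markers goes with an outcome. PCA asks which directions carry the most variance across all samples. Those directions may reflect disease, but they may equally reflect general inflammation, age, assay batch or current treatment, which here follows clinical routine and so differs between patients and stages. Two misreadings are possible:

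- Overlap of the stage groups on the leading components may be read as absence of a profile when the profile lies elsewhere.
- Separation may be read as a disease profile when batch or treatment produced it.

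PCA by itself supplies no null distribution against which to judge either picture. The Mann-Whitney tests do use the stage labels, but they examine one marker at a time. They can list markers; they cannot say whether a combination discriminates, or how well. At stake is the profile part of the objectives, not the detection of single markers.

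**Working it through.** **1. Group sizes.** From Results: 0.30 × 120 = 36 advanced, which reproduces the stated figure, and 120 − 36 = 84 early. The article states no alpha, power, effect size or marker count, so there is no detection rate to reproduce. Every input below other than 84 and 36 is an assumption, with one sample per patient.

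**2. What enters the components.** PCA takes the eigenvectors of the marker covariance matrix. Stage and PFS appear nowhere in that calculation. With group shares 0.3 and 0.7, a mean difference vector δ enters the total covariance only as 0.3 × 0.7 × δδᵀ = 0.21 δδᵀ. Take 92 markers, 10 of them shifted by 0.5 SD:

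- |δ|² = 10 × 0.25 = 2.5, so the group difference adds 0.21 × 2.5 = 0.525 to the variance along δ (one marker has variance 1).
- Shifted markers otherwise independent: variance along δ is 1 + 0.525 = 1.525.
- Shifted markers co-regulated with r = 0.4: (1 + 0.4 × 9) + 0.525 = 5.125, a natural leading component.
- Five unrelated factors, illustrated as blocks of about 16 of the other 82 markers with r = 0.4: each has variance 1 + 0.4 × 15 = 7.0. All five outrank 1.525.

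Whether PCA shows the profile therefore depends on correlations that the article does not give.

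**3. Simulation over a grid.** 40 or 92 markers; 5, 10 or 20 shifted; 0.5 or 0.8 SD; four correlation structures: 2 × 3 × 2 × 4 = 48 non-null scenarios, 200 runs each (Monte Carlo standard error at most √(0.25/200) = 0.035). Component scores were compared between groups by Mann-Whitney with Bonferroni correction. Detection for 92 markers, 10 shifted by 0.5 SD:

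| Correlation structure | PC1-2 | PC1-5 | Any marker, Mann-Whitney with Bonferroni | Group-using global permutation test |
|---|---|---|---|---|
| Independent | 0.54 | 0.66 | 0.74 | 0.96 |
| Shifted markers co-regulated | 0.87 | 0.80 | 0.56 | 0.86 |
| One large unrelated factor | 0.80 | 0.92 | 0.79 | 0.22 |
| Five unrelated factors | 0.10 | 0.12 | 0.76 | 0.66 |

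Over all 48 scenarios:

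- PC1-2 detection ran from 0.06 to 1.00. It was below one half in 12 of 48 (10 of 48 with PC1-5).
- Ten of those 12 had five unrelated factors. The other two had a weak, sparse signal among independent markers (0.36 and 0.20).
- In those ten, Mann-Whitney with Bonferroni still flagged at least one marker in 0.50 to 1.00 of runs.
- With co-regulated shifted markers PC1-2 detection was 0.74 to 1.00; with one large unrelated factor, 0.52 to 1.00.
- Null scenarios gave 0.02 to 0.06.

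**4. A label-using joint model.** Cross-validated ridge regression, again with 92 markers and 10 shifted by 0.5 SD: where several unrelated factors dominate, PC1-2 detected the profile in 6-10% of runs and ridge in 94-100%. With co-regulated shifted markers the order reversed: 89% for PC1-2, 26% for ridge.

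**5. Number of components examined.** In a model with four common factors (400 runs, 92 markers, 10 shifted by 0.8 SD), detection was 8% with two components and 100% with five.

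**6. Single-marker Mann-Whitney power.** Scale both group sizes by 3/π = 0.955: SE = √(1/34.4 + 1/80.2) = 0.204. At two-sided 0.05, 0.5/0.204 − 1.96 ≈ 0.49, power about 0.69; at 0.8 SD, about 0.975. With Bonferroni over 92 markers (0.05/92 = 0.00054), about 0.16 and 0.68.

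**The case against.** The strongest reply is that PCA is not the whole plan. The Mann-Whitney comparison in the same section uses the stage labels, and where PCA failed in the simulations it still found markers in half or more of the runs. The serum-protein part of the primary objective asks for markers and needs no joint method. The article condenses a fuller protocol and refers to further unnamed tools for the protein data. The Introduction describes a coordinated Th1-to-Th2 shift, the kind of structure in which PCA performs well. The article does not limit PCA to two components or say that overlap will be read as no profile; that decision rule belongs to the simulation. No label-using method was better throughout, and the number of 6-month progression events is not given.

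Most of this stands, and it limits the point. A reader might infer that a real multi-marker profile will usually be missed, or that the plan has almost no power. The documents support neither: they give no marker count, correlation or effect size, and in the assumed grid PCA missed the profile more often than not in a minority of scenarios. Nor is it fair to set low PC1-2 detection against near-100% detection by FDR-controlled marker tests, since that comparator is essentially the plan's own Mann-Whitney tests with a multiplicity adjustment.

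The reply does not remove the core. Comparing profiles by PCA is a stated choice, not detail left to another document, and single-marker tests do not supply the missing joint analysis.

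**Conclusion.** The concern holds in a limited form. The one multivariate method named for the profile comparison uses neither stage nor PFS and gives no group test of its own. A joint profile outside the leading components can be missed, and a batch or treatment split can be mistaken for disease. The second risk follows from how PCA works and was not simulated.

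The frequency is unknown. Under the assumed settings PC1-2 detection ranged from 0.06 to 1.00, with correlation structure a main driver. The planned Mann-Whitney tests protect the search for single markers, not the search for a profile. Because ridge beat PCA in some structures and lost to it in others, the evidence supports adding a label-using method alongside PCA and Mann-Whitney, not replacing them. The change is worth making, and with 18 of 120 patients enrolled in December 2023 there is time to make it.

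**What to change.** In the Statistical Analysis section or the SAP:

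- Keep PCA, described as display and quality control (outliers, batch).
- Keep the Mann-Whitney tests, with false-discovery-rate control across the panel.
- Add one pre-specified label-using multivariate analysis, for example penalised regression on the panel. Cross-validate by patient, so that repeated samples from one person stay in the same fold.
- Give a global p-value from permuting the label between patients, within site or batch, and report cross-validated discrimination with its interval.
- Apply it to 6-month progression where the number of events allows, and to stage.

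The cost is wording and some extra analysis on data that are collected anyway. Cross-validated results may look less striking than a PCA plot, and estimates for 6-month progression will be unstable if events are few.

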## Results

Patient inclusion started in 2021 and is still ongoing in December 2023, with 18 patients and 20 healthy controls enrolled. Until December 2023, a total of 2 included patients have declined further participation due to the extra visits in this study. Further, 2 patients have died from MF during this study. The publication of selected translational findings before the publication of the main results of the trial is accepted, and data analysis is in progress.

The evaluation of the stage of the disease will be observed every 3 months according to the TNMB classification, where the shift from one stage to another implies progression or treatment response. After the study, patients will be grouped as either early stage of the disease (IA-IIA) or advanced stage of the disease (IIB-IVB). The patients crossing over from the early stage of the disease to the advanced stage of the disease group will be analyzed both individually and as a group. Approximately 30% (36/120) of patients are estimated to be in the advanced stage of the disease group. The translational samples in the early stage of the disease group will be compared to samples from the advanced stage of the disease group. The treatments directed against MF are documented throughout this study. Excluded patients will be presented along with the final results. Depending on patient numbers, treatment data will be presented descriptively, or if possible, to support data on treatment predictive biomarkers.

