### Conclusions

The BIO-MUSE study is a prospective translational study aiming to identify new prognostic and predictive biomarkers in blood and skin in patients with MF and SS.

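### The named marker analyses (an unadjusted early-v-advanced Mann-Whitney test, with survival only plotted) cannot show prognostic value beyond stage, age, sex and LDH

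*Protocol article*

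**What the plan says.** All references are to the protocol article.

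- **Statistical Analysis.** Marker profiles in early (IA-IIA) and advanced (IIB-IVB) disease are compared "using multivariate analysis with principal component analysis". For single markers, "Individual samples will be compared between the groups using the Mann-Whitney" U test. Other samples are described, and progression-free and overall survival are shown as Kaplan-Meier plots. No adjusted, stratified or regression analysis is named.
- **Results.** The contrast is repeated: "The translational samples in the early stage of the disease group will be compared to samples from the advanced stage of the disease group". Its expected size is given: "Approximately 30% (36/120) of patients are estimated to be in the advanced stage of the disease group".
- **Prognosis of MF and SS.** TNMB stage at diagnosis is ranked as the leading prognostic factor. Male sex and age over 60 are listed for early disease, where the list is called potential, and again for advanced disease: "negative prognostic factors for advanced disease consisting of male gender, aged >60 years, stages B1/B2 and N2/N3, and visceral involvement". A further sentence adds that "large cell transformation in the skin, and elevated lactate dehydrogenase are also identified as adverse prognostic factors".
- **Blood Samples (soluble interleukin-2 receptor, interleukins, TARC).** LDH is measured in the study: "Blood samples in patients will be analyzed for complete blood count, liver and kidney function, lactate dehydrogenase, soluble interleukin-2 receptor".
- **Goals of This Study and Discussion, Conclusions.** The primary objective is markers for 6-month PFS. The study is described as "aiming to identify new prognostic and predictive biomarkers in blood and skin in patients with MF and SS".

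**The concern.** To be a new prognostic biomarker, a marker must tell the clinician something about outcome that the known factors do not. By the article's own account those factors are stage, age, male sex and LDH, and the age and sex findings came from multivariate cohort analyses. The test named for the new markers does not meet that standard. A two-group rank test has no place for a covariate, and principal component analysis and Kaplan-Meier plots do not adjust either.

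The two named routes fail in different ways:

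- In the stage comparison, a serum protein or T-cell subset that varies with age, sex or LDH will differ between groups whenever those factors differ between groups.
- For PFS, no model is named that could separate a marker from stage itself.

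At stake is whether a reported marker is new or a stand-in for something already known. This could matter soon, because the article allows selected translational findings to be published before the main results and says that data analysis is in progress.

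**Working it through.** **1. The plan's own figure.** 0.30 × 120 = 36 advanced patients, which agrees with the article; 120 − 36 = 84 early. The article gives no alpha, power or effect size for this comparison, so nothing else can be reproduced.

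**2. What each named method can adjust for.**

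| Method | Grouping | Covariates |
|---|---|---|
| Mann-Whitney U | early v advanced | none possible |
| Principal component analysis | early v advanced | none |
| Kaplan-Meier plots | not stated | none |

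The separate MF and SS analyses mentioned in the Discussion do not adjust for age, sex or LDH.

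**3. How often a marker with no direct link to stage is flagged.** Simulation with 84 v 36 patients, one value each, two-sided 5% level, 4,000 runs per scenario. The marker equals (effect × known factor) + normal noise, with no direct stage term. Two tests were compared: Mann-Whitney, and a linear regression of the marker's ranks on stage group plus the factors. The imbalances, effects and correlations below are all assumptions.

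*(a) Binary factor such as age over 60 or male sex; prevalence 50% in the early group; marker effect 0.5 or 1.0 SD*

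| Prevalence difference | Mann-Whitney, 0.5 SD | Mann-Whitney, 1.0 SD |
|---|---|---|
| 0 points | 4.5% | 5.8% |
| 10 points | 5.8% | 7.5% |
| 20 points | 7.7% | 14.6% |
| 30 points | 12.0% | 26.1% |

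*(b) LDH higher in advanced stage; correlation with the marker 0.3, 0.5 or 0.7*

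| LDH shift | r = 0.3 | r = 0.5 | r = 0.7 |
|---|---|---|---|
| 0 SD | 4.8% | 5.2% | 4.7% |
| 0.3 SD | 7.7% | 11.4% | 17.3% |
| 0.5 SD | 10.6% | 23.5% | 38.6% |
| 0.8 SD | 22.1% | 49.6% | 76.8% |

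The adjusted rank regression stayed between about 4% and 6% in every scenario.

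**4. Does adjustment also buy power?** For a true stage difference of d = 0.5 SD, the noncentrality parameter is d × √(84 × 36/120) / √(1 − ρ²) / √VIF. Here ρ is the marker-factor correlation, and VIF = 1 + 0.3 × 0.7 × D² for a factor shifted by D SD between groups. Power comes from the noncentral t distribution, an approximation to the rank test.

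- Unadjusted: 0.5 × √25.2 = 2.510, power 70.2%.
- ρ = 0.3, D = 0: 2.510/√0.91 = 2.631, power 74.2%.
- ρ = 0.3, D = 0.5: VIF = 1.0525, 2.631/√1.0525 = 2.565, power 72.0%.
- ρ = 0.3, D = 0.8: VIF = 1.1344, 2.631/√1.1344 = 2.470, power 68.8%.
- ρ = 0.4, D = 0.8: 2.510/√0.84/√1.1344 = 2.571, power 72.2%.

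The gain is clearest when the factor is unrelated to stage, and then there is nothing to correct. Where confounding exists, the gain shrinks, and it can become a loss.

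**The case against.** **The article is condensed.** Covariate sets are commonly left to an analysis plan, which is not shown, and the article nowhere calls Mann-Whitney the main test. This stands as a reason for caution: an adjusted model may exist elsewhere. But the article chose and named its marker test, and that test cannot support the stated claim. The point is the fitness of the named method, not missing detail.

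**The rejections are not errors of the test.** If LDH differs by stage and the marker follows LDH, the marker's distribution does differ by stage, and Mann-Whitney is right to reject. This stands. The rejections mislead only when the question is independent association, and it is the aim of finding new prognostic markers that raises that question.

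**No imbalance is documented.** This also stands. The article lists age, sex and LDH as predictors of outcome and does not say that they differ between stage groups. A reader might infer that the plan will produce false new markers. The text supports only that it could: with balanced factors the test keeps about 5%, and with a 10-point imbalance in age or sex it rises only to about 6% to 8%. Nor does the article call these factors established; its early-stage list is labelled potential.

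**Adjusting a stage contrast does not make a marker prognostic.** This stands and shapes the remedy. The test compares stages, not patients who do and do not progress, so an adjusted stage difference is still a stage marker. LDH may itself reflect disease burden, so conditioning a stage contrast on it may remove real signal. A PFS model without stage would let a marker that only tracks stage pass as new.

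**The work is exploratory.** The article elsewhere speaks of potential biomarkers, and unadjusted screening is a usual first step. That justifies keeping the Mann-Whitney test, not relying on it alone.

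**Conclusion.** The concern holds in a limited form. The named analyses are an unadjusted stage comparison and survival plots. They cannot show that a marker carries prognostic information beyond stage, age, sex and LDH, so a marker that tracks one of these could be reported as new.

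The size cannot be fixed from the article. Under the assumptions shown, the unadjusted flag rate runs from about 5% with no imbalance to about 26% for age or sex (30-point imbalance, 1 SD effect). For LDH it reaches about 77% in the most extreme case tried (0.8 SD shift, correlation 0.7). These are rates for a marker with no direct link to stage; they do not forecast this study's results.

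Two stronger readings are not supported. One is that false markers will follow, because that needs an imbalance nobody has documented. The other is that adjustment improves power, because against 70% unadjusted it gives about 72% or 69% at correlation 0.3 with a 0.5 or 0.8 SD imbalance. The change is worth making because it is cheap and serves the study's stated product. Confidence is moderate, since a fuller analysis plan may already contain such a model.

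**What to change.** Amend the Statistical Analysis section as follows:

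1. Keep the Mann-Whitney test and label it the unadjusted result.
2. Beside it, report a rank-based or log-scale regression of each marker on stage group with age and sex as covariates. Add LDH only in a sensitivity analysis, and not where LDH is the marker tested.
3. Relate each marker to PFS in a regression that includes stage, age, sex and inclusion LDH, again omitting LDH as a covariate where it is the marker. The article does not state the expected number of PFS events; if they are few, limit or penalise the covariates.
4. Call a marker new and prognostic only if it remains associated with PFS in that model. An adjusted stage difference alone should not earn the label.

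The cost is analysis wording, a few degrees of freedom and fewer nominally significant markers. No extra patients or samples are needed: LDH is measured, age is needed for eligibility, stage is assessed every 3 months, and sex is assumed to be recorded at inclusion. The change should be justified by what can be concluded about the markers, not by power.
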